## Abstract

**Background:**

The proposed research aims to test the effects and mechanisms of a six-month yoga-based intervention as an add-on to standard treatment in opioid use disorder (OUD) by conducting a randomized controlled study with the following primary outcome variables: 1) clinical: abstinence (opioid negative urine test), and reductions in pain and craving, and 2) mechanisms: reward circuit activation in response to opioid visual cue craving paradigm, activation in response to a cognitive control task, and resting state functional connectivity through fMRI, and plasma beta-endorphin levels. Secondary outcome variables are perceived stress, anxiety, sleep quality, cognitive performance, pain threshold, buprenorphine dosage and side effects, withdrawal symptoms, socio-occupational functioning, vedic personality traits, heart rate variability, serum cortisol, and brain GABA levels through magnetic resonance spectroscopy (MRS).

**Methods:**

In this single-blinded, randomized, controlled, parallel-group superiority trial with 1:1 allocation ratio, 164 patients with OUD availing the outpatient/ inpatient clinical services at a tertiary mental healthcare hospital in India will be enrolled after giving informed consent. Consecutive consenting patients will be randomly allotted to one of the two groups − yoga arm (standard treatment + yoga-based intervention), or waitlist group (standard treatment alone). Allocation concealment will be followed, the clinicians, outcome assessors and data analysts will remain blind to subject-group allocation. A validated and standardized yoga program for OUD will be used as an intervention. Participants in the yoga arm will receive 10 supervised in-person sessions of yoga in the initial two weeks followed by tele-yoga sessions thrice a week for the next 22 weeks. The wait-list control group will continue the standard treatment alone for 24 weeks. Assessments will be done at baseline, two weeks, 12 weeks, and 24 weeks. Data from all randomized subjects will be analysed using intent-to-treat analysis and mixed model multivariate analysis.

**Dissemination:**

Findings will be disseminated through peer-reviewed publication, conference presentations, and social media.

**Trial registration number:**

The trial has been registered under Clinical Trials Registry-India with registration number CTRI/2023/03/050737.

## Background

Opioid Use Disorder (OUD) is associated with socio-occupational impairments, financial crisis, and adverse health consequences including high mortality rates (due to overdose and suicide)^1^. The National Drug Use Survey (2019) reported a prevalence of 2.06% for opioid use in India, with a higher prevalence in urban metropolitan areas^2,3^. The COVID-19 pandemic has further inflamed this ongoing ‘hidden epidemic’ in many countries including India^4^.

Standard treatment for OUD includes pharmacological management with buprenorphine (μ-opioid receptors partial agonist), methadone (μ-opioid receptors agonist) or naltrexone (μ-opioid receptor antagonist) and psycho-social support^5^. Among them, treatment with buprenorphine or methadone, termed opioid substitution therapy (OST) or medications for opioid use disorders (MOUD) has shown better clinical outcomes. Though generally considered to be safe, the use of OST may be associated with dose-dependent side effects such as respiratory depression, constipation, sleep disturbances, nausea, vomiting, dizziness, tiredness, sweating, sexual dysfunction, and drowsiness^6,7^.

A recent systematic review involving 67 studies published in the last 20 years observed that the mean retention rate with OST was 57% at 12 months which further reduced to 38% at three years^8^. The retention rates reduce even further if the maintenance treatment is with naltrexone or psychosocial support only (in the form of symptomatic treatment with motivational interviewing and relapse prevention treatment)^9^. Studies have found that adding behavioral therapy did not help in improving retention rates in this population and with retention rate rarely exceeding 50% at 12 months; therefore clinicians have called for innovative and culturally sensitive treatment strategies^10–12^. In India, a multi-center study by the All India Institute of Medical Sciences (AIIMS), New Delhi, assessed retention rate with buprenorphine treatment and observed it to be 79% at three months, 70% at six months, and 64% at nine months^13,14^. Another large survey in India on 6,600 opioid-dependent participants reported that 67% of OUD patients tried discontinuing treatment on their own in the past year, and only 14% visited de-addiction centers^1^. Treatment challenges in India include: poor treatment seeking, access barriers, low treatment retention, high relapse rates, lack of personalized, culture, and gender-sensitive interventions, higher cost of medications, and social-stigma associated with treatments^1,10^. The major barrier affecting recovery and low treatment seeking was social stigma followed by physical problems^1^. Similarly, other studies have identified social stigma as the fundamental hindrance in overcoming opioid use crisis^1,15,16^.

The prevalence of chronic pain among adults in India is rising rapidly (19.3% in 2018 as compared to 13% in 2013)^17^. There is an increasing prescription of opioids for non-cancerous chronic pain, which has also led to increasing non-prescription opioid use. Lack of awareness among prescribers and pharmacists, poor legislation and drug trafficking increase abuse liability^18,19^. In patients with chronic pain, greater pain has been shown to predict greater cravings for opioids and subsequent opioid use, and pain coping counseling was shown to suppress this association^20^. Similarly, mindfulness (an important component of yoga practice) has been shown to help reduce craving in opioid users and this buffering may be associated with improved heart rate variability (HRV)^21^.

Several recent meta-analyses have reported the beneficial effects of yoga in chronic pain^22–25^. Yoga practices enhance sympathovagal balance and reduce stress in psychiatric disorders, and this may also be the biological basis for amelioration of withdrawal symptoms of OUD^26,27^. Recent meta-analyses and review articles support the usefulness of yoga as an adjunct in the management of substance use disorders^28–31^. Moreover, yoga is free from social stigma and is culturally acceptable and accessible, particularly in the Indian population^32,33^. It is also well accepted among female participants^32^. Interestingly, 34% of the Indian population who suffered from chronic pain, particularly females, opted for yoga and meditation^17^. Besides this, yoga may enhance pain thresholds^34^ and bring a state of natural ‘high’ by providing deep relaxation and calmness to the mind. This may be mediated through the enhancement of gamma-aminobutyric acid (GABA; the main inhibitory neuro-transmitter)^35^, oxytocin^36^ and endorphin levels^37,38^. Yoga has been observed to be as safe as routine physical exercise^39^.

There are very few studies assessing the effect of yoga in OUD. We could identify only six prospective experimental studies exploring the effects of yoga in OUD patients^40–45^. Out of these, three were randomized controlled trials (RCTs) with six months follow-up, two of them demonstrated the utility of yoga in improving quality of life as an add-on to standard treatment. One pilot study (n = 40) showed that add-on Rajayoga meditation led to better improvement in abstinence at six weeks of follow-up than relaxation and standard care or standard care alone^44^. Another matched controlled study (n = 26) observed add-on yoga to be more effective in reducing perceived stress than standard care alone^41^. Similarly, a feasibility study found add-on yoga to be feasible and more effective in reducing anxiety and pain, and improving mood than add-on health education after 12 weeks^45^. None of the previous studies have noted changes in craving, sleep quality, work and social adjustment, withdrawal symptoms, pain threshold, or buprenorphine dosage. Further, there are no studies exploring possible mechanisms of yoga in this population or the option of utilizing tele-yoga for enhancing clinical outcomes in this population.

### Previous work (feasibility and pilot study)

Our team has been working in the area of medical application of holistic yoga-based lifestyle programs for mental and neurological disorders over the last decade. We have validated tools to assess physical and mental constitutions based on traditional Indian medicine (*prakriti:* physical constitution and *gunas:* mental attributes) for psychiatric patients to design personalized holistic lifestyle programs^46,47^. HB has recently developed, validated, and tested the feasibility of a yoga program for OUD (for both the acute withdrawal phase and maintenance phase)^48^. A functional magnetic resonance imaging (fMRI) paradigm to assess reward circuit activation and craving in response to visual cues related to opioids in OUD patients has been developed (manuscript under preparation). We have been offering tele-yoga services to healthy people for stress management and to patients suffering from mental health disorders for over a year now^49^. In a pilot feasibility study, we found tele-yoga to be feasible and acceptable in patients with substance use disorders including OUD patients^50,51^ and have also observed an increase in plasma endorphin levels immediately after yoga practice in healthy participants^52^. Tele-medicine offered by the National Institute of Mental Health and Neurosciences (NIMHANS), Bengaluru has been found acceptable and feasible for psychiatric patients^53^.

In light of the above, a systematic research plan to understand role of long-term yoga intervention as an adjuvant in the management of OUD is proposed.

## Objectives

### Primary objectives

To evaluate the effect of a six-month add-on yoga-based intervention on opioid abstinence (opioid-negative urine results and negative self-reported frequency of opioid use since last follow-up), pain and craving in patients with OUD as compared to standard treatment alone.To examine the neurobiological underpinnings of yoga in OUD by estimating plasma beta-endorphins and brain hemodynamics in response to opioid-use-related visual cues, the stop signal task and resting state functional connectivity through fMRI.

### Secondary objectives

To evaluate the effect of a six-month add-on yoga-based intervention on perceived stress, pain threshold, sleep quality, cognitive performance (n-back task, Stroop task), work and social adjustment, dosage and side effects of buprenorphine, and yoga-based mental attitudes (*gunas*).To examine the effects of yoga-based intervention on withdrawal symptoms, pain threshold, serum cortisol, brain GABA levels through MRS, heart rate variability and buprenorphine dosage required to score zero on the clinical opiate withdrawal scale (COWS) in patients with OUD during acute withdrawal phase.

### Hypothesis

The yoga-based intervention will serve as a useful adjunct therapy to standard treatment as compared to standard treatment alone in patients with OUD by:

**Primary**-1) improving opioid abstinence, 2) reducing pain and craving, 3) enhancing plasma beta-endorphin levels, and 4) reducing reward system activation in response to visual cue craving paradigm, increasing activation in response to the cognitive control task (stop signal), and increasing coherence in resting state functional connectivity through fMRI.

**Secondary**-1) reducing withdrawal symptoms, disease severity, stress, anxiety, sympathetic arousal as measured by HRV, serum cortisol levels, enhanced brain GABA levels through MRS, cognitive performance (n-back task, Stroop task), reducing dosage and side effects of buprenorphine, and improving sleep quality, pain threshold, and yoga-based mental attitude (*guna profile-sattva, rajas, tamas*).

#### Predictions on mechanisms of action

We hypothesize that yoga will act through reversing the excitatory/ inhibitory imbalance in the CNS, by increasing GABA and parasympathetic activity, and reducing allostatic load (by reducing cortisol and enhancing beta-endorphins). It will also act by enhancing cognition (enhancing response inhibition with associated activation of prefrontal and anterior cingulate cortices during the stop signal task and improving cognitive performance as measured by n-back task and Stroop task) and by reducing craving as demonstrated by clinical assessments and reducing activation of brain regions that are known to be activated in patients with addiction in response to addiction-related visual cues (prefrontal and orbitofrontal regions, cingulate cortices, inferior frontal regions, limbic system including amygdala and ventral striatum including nucleus accumbens). Yoga may also act by improving functional resting brain connectivity and coherence and enhancing grey matter volume in this population.

## Plan for research

### Trial design

Single-blinded, randomized, controlled, parallel group superiority trial with a 1:1 allocation ratio.

### Sample size estimation

For evaluating the primary objectives, the optimal sample size was estimated using the principles and methods for the assessment of primary parameters (abstinence, pain, craving, plasma beta-endorphins and fMRI changes). Based on approximation and estimation from the previous data on the clinical effects of yoga interventions in OUD/other patients with substance use disorder supporting a medium effect size^37,40,43,44^, it was estimated that, for an allocation ratio of one, a sample size of at least 82 OUD patients in each arm (accounting for a potential drop-out rate of 36% at six months^40^ with 60 completing the entire study (for the pre- versus post- comparisons of patients) will be required to detect a two-tailed significant difference of α = 0.01 with an estimated 80% power.

The subset sample size of 50 for imaging studies (in each group − pre as well as post-brain scans) will be sufficient to perform random effect analysis for fMRI BOLD changes with multiple comparison correction using random field theory-based family-wise error correction to control for multiple comparison (http://www.fil.ion.ucl.ac.uk/spm/).

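### The enrolment, drop-out and completer figures cannot all hold: 82 per arm with 36% drop-out leaves about 52 completers, not 60

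*Protocol article*

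**What the plan says.** The section on sample size estimation gives one calculation for the trial. It requires "at least 82 OUD patients in each arm (accounting for a potential drop-out rate of 36% at six months", then continues "with 60 completing the entire study (for the pre- versus post- comparisons of patients". The significance level is 0.01 two-tailed, power is 80% and allocation is 1:1. The effect size is called medium, with no number. The Methods part of the abstract gives the matching total, "164 patients with OUD". A separate sentence covers the fMRI work: "The subset sample size of 50 for imaging studies", qualified as applying in each group and to scans both before and after the intervention.

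**The concern.** The sentence presents 82 as already allowing for 36% loss and as yielding 60 completers. A correct allowance divides the number needed at the end by the retention proportion. The 82 looks like the result of adding 36% of the completers instead, which always gives too few patients.

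This is the only sample size justification in the article, and its power statement is attached to the 60. If the protocol's own drop-out rate is right, the completer-based power is lower than stated. If 60 completers is right, the stated drop-out rate is wrong. The section on data analysis also lets the interim results inform a sample size adjustment, so the planning figures need to be sound before anyone compares observed retention with them.

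**Working it through.** **Inputs.** From the section on sample size estimation: 82 per arm, 36% drop-out at six months, 60 completing, two-sided alpha 0.01, power 80%, ratio 1:1. From the abstract: 164 in total. The 60 is read as per arm; step 3 tests the other reading.

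1. **Reproducing the 82.** Multiplying: 60 × (1 + 0.36) = 81.6, rounded up to 82. Dividing: 60 / (1 − 0.36) = 60 / 0.64 = 93.75, rounded up to 94. Only the multiplied form gives the protocol's figure.

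2. **Working forward from 82.** 82 × 0.64 = 52.48, about 52 completers per arm. In total, 164 × 0.64 = 104.96, about 105, against 2 × 60 = 120. The shortfall per arm is (60 − 52.5) / 60 = 12.5%.

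3. **Other readings.** The drop-out rate at which 82 yields 60 is 1 − 60/82 = 26.8%. If 60 were the total over both arms, it would still not fit, since 36% drop-out leaves about 105 of 164.

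4. **Effect on power.** The protocol names no test and gives no numerical effect size, so this step assumes a between-arm two-sample comparison of a continuous outcome among completers. With the normal approximation, the detectable standardised difference is d = (z₀.₉₉₅ + z₀.₈₀) × √(2/n) = (2.576 + 0.842) × √(2/n).

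| Completers per arm | d, normal approximation | d, t-test |
|---|---|---|
| 60 | 0.624 | 0.633 |
| 52 | 0.670 | 0.681 |

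For the effect that 60 per arm detects with 80% power, 52 per arm gives about 73% by either method.

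5. **If medium meant d = 0.5** (an assumption), power would be about 55–57% with 60 per arm and 47–49% with 52. This shows that the 60 cannot be reproduced from d = 0.5 under this test. That is a separate matter, and the drop-out inconsistency needs no effect size to establish.

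6. **Imaging.** If 50 means patients with both scans, 50 / 0.64 = 78.1, so about 78 of the 82 in each arm would have to be scanned at baseline. The expected 52 completers per arm could just supply 50 pairs.

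**The case against.** The inconsistency itself has no good answer in the document, but several points limit what may be built on it.

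- **The shortfall is conditional.** A reader might infer that the sample behind the power statement will not exist. The document does not support that: the shortfall follows only if 36% drop-out occurs. The Background cites 70% six-month retention on buprenorphine in India, which would leave 82 × 0.70 = 57.4 per arm and about 78% power for the same effect. That figure is treatment retention, not trial retention, so it is context only, and it still falls short of 60.
- **Completers are not the whole analysed sample.** The section on data analysis plans an intent-to-treat mixed model on all randomised participants. Table 1 schedules assessments at two weeks and three months, so patients who leave later still contribute. This stands, and it makes 73% a completer-based figure. It does not rescue the sample size sentence, which itself counts completers.
- **The test is assumed.** The protocol describes the 60 as serving comparisons before and after treatment. The shift from 0.63 to 0.68 depends on the assumed t-test and does not carry over to abstinence, which is binary.
- **The cause is inferred.** The match with 60 × 1.36 is close, but a misstated drop-out rate is also possible. The 36% comes from a cited study that is not at hand.
- **Imaging is not a shown error.** A reader might infer that the subset shrinks from 50 to 50 × 0.64 = 32 per group. That requires 50 to be the number scanned at baseline, whereas the wording more naturally means 50 with both scans. MRI contraindications exclude patients from the whole trial, so scanning about 78 of 82 is not contradictory. A condensed article may also leave the imaging allowance to the full protocol.

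**Conclusion.** The point holds for the main calculation. The protocol's 82, 36% and 60 contradict one another, and nothing elsewhere in the article reconciles them. Taking 82 and 36% as given, about 52 per arm are expected to complete, roughly 7 or 8 fewer than stated. Under the assumed t-test among completers, power for the effect behind the 80% claim drops by about 7 percentage points. The true loss may be smaller because of the mixed model or better retention. The contradiction is certain; its effect on power is modest and rests on those assumptions. The imaging subset calls only for clarification.

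**What to change.** Make the sentence consistent in one of two ways:

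- keep 82 per arm and 36%, state about 52 expected completers per arm, and give the power or detectable effect for that number, naming the test and the effect size; or
- keep 82 per arm and 60 completers, and state and justify a drop-out rate of about 27%.

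Both cost only wording, although the first makes the stated power less favourable. Keeping both 60 completers and 36% is a design change: 94 per arm, 188 in total, which is 24 more patients than the planned 164.

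For imaging, add a clause saying whether 50 per group is the number scanned at baseline or the number with both scans. If it is the latter, give the baseline number this requires, about 78 per arm at 36% drop-out.

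### The stated 80% power at two-sided alpha 0.01 cannot be reproduced for the between-arm comparison, and the only comparison the sizing names is pre- versus post-

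*Protocol article*

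**What the plan says.** The Trial design section describes a "parallel group superiority trial with a 1:1 allocation ratio". The Objectives and Hypothesis sections set every primary outcome (abstinence, pain, craving, beta-endorphin, fMRI) as a comparison with standard treatment alone.

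The Sample size estimation section refers to earlier yoga studies "supporting a medium effect size" and, "for an allocation ratio of one", asks for at least 82 patients in each arm. It allows for 36% drop-out at six months and expects 60 to complete. The 60 completers are then described as being "for the pre- versus post- comparisons of patients". The section says that these numbers "will be required to detect a two-tailed significant difference of α = 0.01 with an estimated 80% power".

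The section gives no numeric effect size, standard deviation, event rate, correlation or test. The Data analysis section plans an intent-to-treat analysis of all randomised participants with mixed models. Table 1 schedules abstinence, pain and craving at four visits, and beta-endorphin and fMRI at three.

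**The concern.** A power statement is useful only if it refers to the comparison that answers the primary question. Here that is the difference between arms. A change from before to after within one arm does not test the add-on effect, because both arms continue medication and psychosocial support and may both improve. Yet pre versus post is the only comparison the sizing paragraph names, and the 80% does not follow for the between-arm comparison under the usual reading of a medium effect.

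Two things are at stake. A non-significant result could be taken as evidence against a medium effect when the trial may have had only about an even chance of detecting one. Also, the Data analysis section allows the sample size to be adjusted after an interim analysis at 50% of the target, and a planning figure that belongs to no stated comparison is a poor basis for that decision.

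**Working it through.** **Inputs from the protocol article:** two-sided alpha 0.01; power 80%; allocation 1:1; 82 randomised per arm; 36% drop-out; 60 completers (read as per arm).

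**Assumption:** medium means d = 0.5. Other values are shown below.

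**1. Trying to reproduce the stated size between arms.** With the normal approximation, n per arm = 2(z₀.₉₉₅ + z₀.₈₀)²/d² = 2(2.576 + 0.842)²/0.25 = 93.4, so 94. With the noncentral t it is 96 evaluable per arm. Neither 60 nor 82 comes out. Allowing for 36% drop-out, 96/0.64 = 150 would have to be randomised per arm.

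**2. Power of the unadjusted two-sample t-test.** The noncentrality is d√(n/2) on 2n − 2 degrees of freedom.

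| Evaluable per arm | Source | Noncentrality at d = 0.5 | Power, d = 0.4 | Power, d = 0.5 | Power, d = 0.65 | d for 80% power |
|---|---|---|---|---|---|---|
| 52 | 82 × 0.64 = 52.5 | 2.55 | 28% | 47% | 75% | 0.68 |
| 60 | as stated | 2.74 | 34% | 55% | 82% | 0.63 |
| 82 | no drop-out | 3.20 | 48% | 72% | 94% | 0.54 |

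The 52 appears because 36% drop-out from 82 does not leave 60; 60 of 82 would mean 27% drop-out. That mismatch is a separate matter. The shortfall at d = 0.5 is present with 60, and with 82.

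**3. Adjusting a continuous outcome for its baseline.** The effective difference is d/√(1 − r²), where r is the baseline-to-outcome correlation (assumed). At d = 0.5:

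- r = 0.5: 0.5/√0.75 = 0.577, giving 71% power (60 per arm) or 63% (52).
- r = 0.6: 0.5/√0.64 = 0.625, giving 79% (60) or 71% (52).

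With 60 per arm, 80% therefore needs r of about 0.6. With 52 it needs nearly 0.7.

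**4. The pre- versus post- reading.** A paired t-test with a standardised change of 0.5 has noncentrality d√n on n − 1 degrees of freedom. It needs 51 patients for 80%; 52 give 82% and 60 give 88%. Then 51/0.64 = 79.7, or 80 randomised, which is close to 82 but does not yield the stated 60.

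**5. Abstinence.** This is a difference in proportions. With an assumed 50% abstinent under standard treatment, 80% power at two-sided alpha 0.01 (normal approximation, pooled variance under the null) requires 79.5% abstinent with 60 per arm, or 81.4% with 52. These are differences of about 29 and 31 percentage points.

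**The case against.** The strongest reply is that the unadjusted single-visit test on completers is not the planned analysis. The protocol plans mixed models on everyone randomised, and several between-arm routes reach or pass 80% with 60 per arm:

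- Baseline adjustment at r = 0.6 gives 79%.
- A group effect averaged over four visits (f = 0.25, within-patient correlation 0.5) has noncentrality 0.0625 × 120 × 4/(1 + 3 × 0.5) = 12, which gives 79.9% and almost exactly matches 60 per arm.
- A baseline-adjusted mean of the three later visits, with a constant d = 0.5 and correlation 0.5, would give about 95%.

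Part of this stands. The article gives no number for the effect, so neither 55% nor 47% can be called the trial's actual power. But the correlations and averaging that these routes need are not stated either. The four-visit average includes baseline, where randomisation leaves no effect to find, so an average of 0.5 over four visits means 0.5 × 4/3 = 0.67 at each later visit. The three-visit mean assumes the full effect by week two, and beta-endorphin is not measured then. Baseline adjustment would help binary abstinence little.

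A reader might also infer that a paired calculation produced the shortfall. The wording makes that possible, but the documents do not show it. A paired test at d = 0.5 needs 51 and not 60, an allocation ratio has no role in a paired test, and the parenthesis may only mean patients with both baseline and final data. Nor does the article plan to test the add-on effect by within-arm change: its hypotheses are between arms, and the imaging model has group as a between-subject factor.

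**Conclusion.** The point holds in this form: from the inputs printed in the Sample size estimation section, 80% power at two-sided alpha 0.01 for a medium effect is not reproducible for the between-arm comparison, and the one comparison named there does not test the add-on effect.

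The size of the gap depends on assumptions. For an unadjusted test at d = 0.5, power is 25 percentage points below the claim with the stated completers (55%), 33 points below with the completers that the stated drop-out implies (47%), and 8 points below with no drop-out at all (72%). An effect of about 0.63 to 0.68, or a baseline correlation of about 0.6 with 60 per arm at d = 0.5, would bring the figure to roughly 80%. These would be legitimate assumptions if stated and justified; at present they are absent. The arithmetic is firm, but the reading of medium as 0.5 is a convention.

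**What to change.** In the Sample size estimation section, replace the pre- versus post- wording with the between-arm contrast at 24 weeks. Restate the power or the detectable effect for that contrast, giving the numeric effect size, the test and any assumed correlation. For example, unadjusted, 80% power at two-sided alpha 0.01 corresponds to d = 0.63 with 60 completers per arm, or d = 0.68 with 52.

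Give abstinence its own figure as a difference in proportions, with the assumed control rate written down. For pain, craving and beta-endorphin, name the baseline-adjusted between-arm difference; Table 1 already collects these baselines. If a mixed-model gain is claimed, state the visits used and the correlation.

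The cost is protocol wording only, with no new data or visits. The stated power may become less favourable. If the sponsor wants 80% for an unadjusted d = 0.5 instead, the price is about 150 randomised per arm at 36% drop-out.
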